
**Figure 1 F1:**
[figure not shown]
Participant flow diagram. FBC, full blood count; OPERA, Optimising Primary thErapy in pRimAry; PBC, primary biliary cholangitis; POCBP, people of childbearing potential; U&Es, urea and electrolytes; UDCA, ursodeoxycholic acid; URS, UDCA Response Score; GGT, gamma-glutamyl transferase; EQ-5D-5L, EuroQoL 5 Dimensions 5 Levels.

### Optional liver biopsy sub-study

Liver biopsy pre and post therapy will be undertaken in a subgroup of participants (n=30) as part of an optional sub-study. Participants in the sub-study will be allocated in a ratio of 1:1 placebo:intervention via stratified randomisation. The procedure will be performed as for a normal clinical biopsy according to local centre practice. The blocks will be sectioned and stained for immuno-histochemistry analysis for senescence markers.

### Pharmacovigilance

All adverse events (AEs) occurring from consent to the end of trial participation will be recorded in the CDMS as well as the participant’s medical notes (with the exception of protocol specific reporting exclusions). AEs will be MedDRA coded; MedDRA, the Medical Dictionary for Regulatory Activities terminology, is the international medical terminology developed under the auspices of the International Council for Harmonisation of Technical Requirements for Pharmaceuticals for Human Use (ICH). MedDRA trademark is registered by ICH.

AEs meeting the seriousness criteria (serious AEs (SAEs)) will be reported within 24 hours of awareness. A SAE for the OPERA trial is any untoward medical occurrence that:

Results in deathIs life-threatening*Requires inpatient hospitalisation or prolongation of existing hospitalisationResults in persistent or significant disability/incapacityConsists of a congenital anomaly or birth defectOther important medical events that jeopardise the participant or require intervention to prevent one of the above consequences

*Life-threatening refers to an event in which the participant was at immediate risk of death at the time of the event; it does not refer to an event which hypothetically might have caused death if it were more severe. The assessment of expectedness will be performed by the CI against the approved Reference Safety Information (RSI) for the trial (SmPC for OCALIVA 5 mg, section 4.8 - Undesirable Effects). Suspected Unexpected Serious Adverse Reactions (SUSARs) will be reported to the MHRA (Medicines and Healthcare products Regulatory Agency) and REC (Research Ethics Committee) within the required regulatory reporting timelines.

In the event of a trial participant or their partner becoming pregnant during their participation in the trial, this will be reported within 24 hours of awareness.

Emergency unblinding is available via the 24-hour web-based randomisation system for valid medical or safety reasons.

### Discontinuation and withdrawal

Participants have the right to discontinue trial treatment or withdraw from the trial at any time without detriment to their care. Participants choosing to discontinue trial treatment will be invited to complete all trial follow-up visits and assessments. Participants choosing to withdraw from the trial will not take part in any further trial activity. Data collected up to the point of withdrawal will be retained and included in analysis, as per consent for the trial. At the point of withdrawal, participants can decide whether or not to allow the research team to continue to collect routine NHS data from their hospital records up to the 52-week visit time point. Participants who withdraw from the trial after randomisation will not be replaced.

NHS Indemnity applies in the OPERA trial and ensures compensation to those who suffer harm from trial participation but does not offer no-fault compensation.

### Data management and confidentiality

Participant data will be entered by site staff into a trial-specific CDMS, Sealed Envelope’s Red Pill (Sealed Envelope, London, UK). Access to the CDMS will be via individual, password-protected roles and limited to the user’s site and delegated duties. All potential participants will be assigned a unique Participant ID by site staff; the Participant ID will be used to add participants to the CDMS and will remain in place when participants are randomised into the trial. Personal data will be regarded as strictly confidential with all trial records and Investigator Site Files being stored at site with restricted access. Written consent will be obtained from participants to allow access to their hospital records.

Data will be handled, computerised, stored and archived in accordance with the General Data Protection Regulation (2018) and the latest Directive on Good Clinical Practice (GCP) (ICH-E6 (R3)). Newcastle Clinical Trials Unit (NCTU) staff will monitor the trial conduct and data integrity in accordance with the trial Monitoring Plan.

### Analysis

The primary analysis will be in the intention-to-treat (ITT) population and repeated in the per-protocol (PP) populations. There will be three analysis populations in total:

ITT: Includes all participants who were randomised, analysed according to their allocated group. This extends to participants who are found to be ineligible post-randomisation and participants who, despite having withdrawn from treatment, have consented to continued follow-up.PP: Includes all participants who were randomised, received assigned treatment and achieved an 80% compliance rate to the intervention by week 26. Treatment compliance will be assessed using the tablet count of returned medication and calculated as the number of tablets taken divided by the number of tablets expected to have been taken.Safety population: Includes all participants who were randomised and received at least one dose of OCA or placebo.

All analyses will be described in a Statistical Analysis Plan, to be finalised prior to trial statisticians receiving any unblinded data. For the analysis of the primary outcome, we will use the augmented binary method.^25^ This will consist of fitting a bivariate normal regression model to the alkaline phosphatase (ALP) and bilirubin values (expressed as a percentage of the ULN). The model will include parameters representing the treatment effect and the effect of baseline measurements of the respective component. Model parameters will then be used to estimate the OR of the normalisation rate between arms. A 95% CI and p value for testing the null hypothesis of no difference between arms will be obtained via the delta method and Wald test, respectively. As a secondary analysis, we will also analyse the normalisation rate as a binary outcome using a logistic regression with the same parameters. Continuous secondary outcomes will be analysed with linear mixed effects models, adjusting for baseline. Binary outcomes will be analysed with a logistic regression model (and, where the outcome is defined by a dichotomised continuous variable, with the augmented binary method). Should there be a non-negligible level of missing data in the primary outcome (>5% loss to follow-up), we will consider performing a sensitivity analysis using multiple imputation techniques. The linear mixed effects model accounts for missing outcome data under a missing at random assumption.

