Clinical review: Clinical history relevant to PBC and this trial, adapted according to the type of visit. At screening, this will include demographics, a detailed clinical review of PBC and its symptoms as well as medication history. At subsequent visits, this will include any changes in the history since screening, including any symptom changes or de novo symptom development and/or difficulties with taking medication.Clinical examination: A full physical examination will be conducted, including examination of skin; lymph nodes; eyes; ears; nose; throat; respiratory; cardiovascular; abdomen; musculoskeletal; neurological assessment; mental status assessment. Bodyweight will also be measured.Vital signs: Heart rate, blood pressure and temperature will be recorded.Blood sampling: A blood sample will be taken (maximum 50 mL) at times specified in figure 1 for the following assessments:Renal function: urea, creatinine and serum electrolytes.Liver biochemistry: alanine transaminase (ALT), aspartate aminotransferase (AST), alkaline phosphatase (ALP), total bilirubin, direct bilirubin, gamma-glutamyl transferase (GGT), albumin.Cholesterol (total cholesterol, Low Density Lipoprotein (LDL), High Density Lipoprotein (HDL), total:HDL ratio and triglycerides).Full blood count (haemoglobin, platelets and white cells—neutrophils and lymphocytes).Clotting: Prothrombin time and activated partial thromboplastin time.Experimental chemokine blood marker.Optional biobank blood sample.Clinical samples will be analysed in the clinical laboratories of the trial site, following standard local laboratory procedures.All chemokine samples will be analysed simultaneously at the end of the trial. All chemokine assessments will be performed in a fully blinded manner, with regard to treatment group and pre-therapy and post-therapy timing.There are three optional additional blood samples (baseline, visits 4 and 5) for use in future PBC research.Urine sampling: Participants will be asked if they are willing to provide consent to give two optional urine samples (baseline and visit 5).URS: Predicts the likelihood of someone responding to UDCA.^10^ URS must be calculated using the OPERA URS calculator that is provided as part of this clinical trial and available here: https://www.mat.uniroma2.it/~alenardi/URS.html.The URS calculator considers three different ‘cut-offs’ to define UDCA response. In this trial, we use the version that considers the outcome of interest to be biochemical remission (ie, ALP <1× upper limit of normal (ULN)). Based on the URS value, a predicted probability of biochemical remission can be calculated. For the purposes of trial eligibility, URS will be calculated using blood results prior to treatment with UDCA.Pregnancy testing: For people of childbearing potential, a pregnancy test will be carried out during the trial screening visit.EQ-5D-5L: A five-item, validated general quality of life measure from which health utility can be calculated.^26^PBC-40: A disease-specific, patient-derived multidomain quality of life measure. It has six domains relating to fatigue, cognitive symptoms, social function, emotional status and general symptoms.^5^Patient Health Questionnaire: A non-validated 5-point scale to assess health status perceived by participants in response to the trial medication at 26 and 52 weeks.Transient elastography (fibroscan): Clinically validated non-invasive tool used to assess liver stiffness; a surrogate marker of liver fibrosis.Compliance: Compliance regarding IMP will be checked at the interim telephone visit (4 weeks after taking IMP at day 0) and followed up at a clinic visit at week 12 and week 26. IMP compliance will be recorded in the Clinical Data Management System (CDMS). Pharmacy will count and record all returns received from each participant on the IMP accountability log. An accountability check will also be performed as part of on-site monitoring visits.

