### Sample size calculations

The proposed sample size is 106 (powered at 48 per group for two groups with a 10% increase for drop out). This sample size has been derived based on an analysis of the extensive UK-PBC dataset undertaken as part of the design of this trial, as well as published Dutch and Global PBC analyses.^12 27 28^ Based on the patients who would fulfil the eligibility requirements, the normalisation rate at 12 months post-UDCA was 17%. To account for the placebo effect, we assume the 6 month control arm normalisation rate will be 20%. We power to detect a significant difference when the experimental arm has a 45% normalisation rate. If the normalisation rate were analysed as binary, then 144 patients would be required to attain 90% power (5% two-sided error) with a two-arm design, not allowing for dropout (Pearson χ^2^ test). As the normalisation rate is defined in terms of ALP and bilirubin values (continuous variables) being below an upper limit, the augmented binary method^25^ can be used. This method makes inference on the normalisation rate but uses the continuous data on ALP and bilirubin to improve the precision. Simulation studies that resampled data from the UK-PBC data to simulate trials under the null and alternative hypotheses were used to determine that with the augmented binary analysis, the power is 90% when the number of patients per arm is 48 (which we increase by 10% to 53 to account for 10% dropout). Thus, the sample size required is 106.

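### As written, the primary model cannot use a participant who has no week-26 values; adding visit-4 ALP and bilirubin, if collected, would protect the odds ratio when response-related dropout differs between arms

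*Protocol article*

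**What the plan says.** All references are to the protocol article.

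- **Endpoint (Table 1).** Remission is normal ALP and total bilirubin at 26 weeks, visit 5.
- **Primary model (Analysis).** The augmented binary method consists of "fitting a bivariate normal regression model to the alkaline phosphatase (ALP) and bilirubin values (expressed as a percentage of the ULN"). Its terms are treatment and the baseline of the same component. No visit term and no intermediate value is named.
- **Population (Analysis).** The primary population is ITT, meaning everyone randomised.
- **Missing primary outcome (Analysis).** If loss exceeds 5%, a multiple-imputation sensitivity analysis will be considered. The next statement, "The linear mixed effects model accounts for missing outcome data under a missing at random assumption", concerns the mixed model, which is named for continuous secondary outcomes.
- **Withdrawal (Discontinuation and withdrawal).** "Data collected up to the point of withdrawal will be retained and included in analysis". Participants who only stop trial treatment are invited to all remaining visits. Those who withdraw may allow routine NHS data to be collected up to week 52.
- **Week 12 (Intervention; Participant follow-up assessments).** Visit 4 is a clinic visit at week 12. Sampling times are in Figure 1, which is not shown. The text adds: "There are three optional additional blood samples (baseline, visits 4 and 5) for use in future PBC research".
- **Planned loss (Sample size calculations).** 10%.

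**The concern.** A bivariate model has one ALP and one bilirubin outcome per person. Someone with neither value at week 26 drops out of its likelihood, whatever was measured at week 12. The estimate is then valid only if loss depends on nothing beyond arm and baseline. If loss also depends on the week-12 response, and does so differently in the two arms, those left at week 26 are selected differently and the odds ratio shifts. Loss after visit 4 could plausibly differ by arm: the step-up at that visit depends on tolerability, and the Introduction names pruritus as a concern of the regimen. Whether such loss would also track ALP is unknown.

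At stake are the size of the primary odds ratio and, to a lesser degree, its precision in a trial of 106.

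**Working it through.** **1. The plan's own figures.** With 20% v 45%, two-sided 5% and 90% power, the pooled Pearson formula with mean rate 0.325 gives

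n per arm = [1.96·√(2·0.325·0.675) + 1.2816·√(0.20·0.80 + 0.45·0.55)]² / 0.25² = (1.298 + 0.818)² / 0.0625 = 71.7, so 72.

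That is 144 in total and agrees with "144 patients would be required to attain 90% power (5% two-sided error) with a two-arm design". The statement that "the power is 90% when the number of patients per arm is 48" comes from resampling UK-PBC data and cannot be reproduced from the article. Inflation: 48 × 1.1 = 52.8, so 53. After 10% loss, 53 × 0.9 = 47.7 per arm remain, against 48 needed.

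**2. True odds ratio.** (0.45/0.55)/(0.20/0.80) = 3.27.

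**3. Simulation.** 53 per arm, 2,000 trials per setting, one dominant normal ALP-type marker. Assumed, not in the article: baseline–week 26 correlation 0.6; 70% of the effect present at week 12; week 12–week 26 residual correlation ρ of 0.5 to 0.9; loss after week 12.

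- *Stated model:* regress week 26 on arm and baseline in those observed at week 26. For arm k, p_k is the average over participants of Φ[(c − α − βk − γ·baseline)/σ], where c is the threshold. Log OR = logit p₁ − logit p₀.
- *With week 12:* regress week 12 on arm and baseline in everyone, and week 26 on arm, baseline and week 12 in those observed. Substitute the first into the second, with variance s₂² + g²s₁², where g is the week-12 coefficient, and form the same log OR.

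Results at 10% loss overall:

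| ρ | SD of log OR, random loss: stated / with week 12 (ratio) | Stated model, same mechanism in both arms: bias (OR) | Stated model, poor responders leave OCA only: bias (OR) | With week 12, same OCA-only loss: OR |
|---|---|---|---|---|
| 0.5 | 0.299 / 0.295 (1.014) | +0.003 (3.28) | +0.086 (3.57) | 3.29 |
| 0.7 | 0.293 / 0.286 (1.024) | −0.001 (3.27) | +0.135 (3.74) | 3.33 |
| 0.9 | 0.301 / 0.288 (1.045) | +0.002 (3.28) | +0.156 (3.83) | 3.29 |

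The Monte Carlo error of a mean log OR is about 0.30/√2000 = 0.007. The dropout slope was 1 in the same-mechanism setting and 1.5 in the OCA-only setting. If the mechanism ran in opposite directions in the two arms, the stated model gave 3.91 to 4.54. With week 12 included, bias was at most 0.03 on the log scale in every setting.

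**4. Precision in context.** With no loss the SDs were 0.282, 0.277 and 0.284, so 10% random loss costs the stated model about 6% (0.299/0.282 = 1.06). This is close to √(53/47.7) = 1.054, which the inflation to 53 is meant to cover. Week 12 would recover 1 to 5 points of it. If the week-12 model had exactly 90% power (1.96 + 1.2816 = 3.2416), the stated model would have Φ(3.2416/1.014 − 1.96) = 89% to Φ(3.2416/1.045 − 1.96) = 87%. Only these relative figures should be used: the one-marker simulation gives about 98% power in absolute terms, which is not comparable with the UK-PBC resampling.

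**5. A second set of assumptions.** Correlations: baseline–week 26 0.5, baseline–week 12 0.6, week 12–week 26 0.7 to 0.9; 80% of the effect at week 12. Variance ratios were 1.04 to 1.09, or √1.04 = 1.02 to √1.09 = 1.04 in SD. With 5% loss on placebo and 15% on OCA, where OCA leavers tend to have high week-12 ALP, the stated model gave OR 3.92 and the joint model 3.31. With no true effect and the same loss, rejection was 8.1% v 4.8%, using the empirical SD. If 10% were lost in each arm and only the placebo leavers tended to have high week-12 ALP, the stated model gave 3.04 against 3.31. The bias can go either way.

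**The case against.** - **Week-12 ALP and bilirubin are not documented as held.** This stands. The schedule is in Figure 1, and the optional visit-4 sample is for future research. The word additional suggests that routine bloods are drawn at that visit, but the point remains conditional.
- **Stopping OCA is not the same as missing week 26.** This stands. A reader might infer that everyone who stops treatment after visit 4 leaves the primary analysis. The Discontinuation and withdrawal section keeps them in follow-up, and routine NHS data may supply a value for some who withdraw.
- **The bias is scenario-dependent.** This stands. A reader might infer that any response-related dropout biases the odds ratio, but an equal mechanism in both arms gave almost none. Loss was also generated from week-12 values, so the joint model is favoured by construction.
- **The precision loss is budgeted.** Largely right. A reader might infer that the planned power is lost; 47.7 against 48 per arm says otherwise. What is forgone is a small gain.
- **The alleged contradictions are inference.** This stands. Safety and secondary analyses can honour the promise about data before withdrawal. The article also does not say that the mixed model for ALP and bilirubin reduction uses week 12, so it is not shown that secondary (b) would be analysed on more people than the primary outcome.
- **The SAP may settle this.** Possibly, but the article itself fixes the bivariate model and its terms, and leaves imputation as something to be considered even though planned loss is twice the 5% trigger.

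**Conclusion.** The concern holds in a limited form. As the article states the primary model, a randomised participant with neither week-26 value adds nothing to the treatment comparison, and the only stated remedy is an optional sensitivity analysis.

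If visit-4 biochemistry exists, leaving it out costs about 1% to 5% in the SD of the log OR at 10% loss. The bias is negligible when dropout relates to response in the same way in both arms. It is material when the relation differs: OR 3.57 to 3.83 against 3.27 if poor responders leave the OCA arm only. These sizes rest on assumed correlations, a single marker, and loss driven by the week-12 value. The documents do not show that such loss will occur or in which direction. This is an inexpensive gain in robustness, not a flaw that invalidates the design.

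**What to change.** Before the trial statisticians receive unblinded data, confirm that ALP and bilirubin are taken at visit 4. If so, fit the augmented binary model jointly to visit-4 and visit-5 ALP and bilirubin: four outcomes, unstructured covariance, and visit-specific treatment and baseline effects. Use maximum likelihood in all randomised participants with any post-baseline value, and still derive remission at visit 5 only.

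At the least, commit to multiple imputation, rather than leave it to be considered, with the visit-4 values among the predictors.

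Cost: no new data; a few more covariance parameters; a simulation recheck of type I error and power at 106, because the 90% was established for the stated method; and an amendment to the protocol's model sentence. Participants lost after visit 4 would be predicted from their own week-12 values. That is still an assumption, but a weaker one than treating them as like the observed members of their arm with the same baseline.

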### Randomisation

Eligible patients will be randomised to one of two treatment arms, OCA or matched placebo, in a 1:1 ratio. Treatment allocation is double blind, though emergency unblinding is available for medical or safety reasons where it is necessary for the treating clinician to know the participants’ treatment allocation.

The allocation sequence will be computer-generated, using a random permuted block design; blocks might vary in size and will not be disclosed, to ensure concealment. Patients will be randomised in a ratio of 1:1 (placebo: intervention), with stratification according to consent to the biopsy sub-study (to ensure equal allocation between arms in the sub-study).

Randomisation will be carried out using the trial database, Sealed Envelope (London, UK), a central, secure, 24-hour, web-based randomisation system with concealed allocation.

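### Biopsy-sub-study consent stratifies the randomisation but is absent from the stated terms of the primary and logistic models: a minor, conservative mismatch

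*Protocol article*

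**What the plan says.** The Randomisation section of the protocol article describes the allocation as follows: "The allocation sequence will be computer-generated, using a random permuted block design". It is 1:1, "with stratification according to consent to the biopsy sub-study (to ensure equal allocation between arms in the sub-study"). No other stratification factor is named.

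The Analysis section gives the content of the primary bivariate normal model: "The model will include parameters representing the treatment effect and the effect of baseline measurements of the respective component". The confidence interval and p value are model-based; they "will be obtained via the delta method and Wald test, respectively". For the supporting analysis, "we will also analyse the normalisation rate as a binary outcome using a logistic regression with the same parameters". Continuous secondary outcomes get linear mixed models, for which baseline is the only adjustment named. No section places biopsy consent in any model or gives a reason for leaving it out. The same section adds: "All analyses will be described in a Statistical Analysis Plan, to be finalised prior to trial statisticians receiving any unblinded data". That plan is not at hand.

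**The concern.** Permuted blocks within strata hold the arms nearly balanced on biopsy consent, so differences between strata contribute almost nothing to the true sampling variance of the treatment comparison. A normal model without the factor does not use this. It counts between-stratum differences as residual noise and reports a standard error that is too large, by an amount that depends on how strongly consent predicts the outcome after baseline adjustment.

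What is at stake is a little precision. The trial's case for its reduced sample rests on extracting more precision from the data, and 48 per arm is the number at which its simulations reach 90% power. Giving some of that back for want of a covariate already recorded for allocation is avoidable.

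**Working it through.** **Inputs from the article.** Biopsy stratum about 30 (Optional liver biopsy sub-study) of 106 randomised, so p = 30/106 ≈ 0.28. Control rate 20%, experimental rate 45%, two-sided 5%, 90% power, 144 patients for a binary analysis, 48 per arm for the augmented binary method (Sample size calculations).

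**Assumption.** The documents give no figure for how far consent predicts outcome. It is written below as a shift of d residual SDs between strata after baseline adjustment, and varied.

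**1. The plan's own figure.** Pooled two-proportion formula with mean rate 0.325: n = [1.960·√(2·0.325·0.675) + 1.282·√(0.20·0.80 + 0.45·0.55)]² / 0.25² = (1.298 + 0.818)² / 0.0625 ≈ 71.7, so 72 per arm and 144 in total. The stated 144 reproduces. The 48 per arm comes from resampling UK-PBC data and cannot be checked from the article. The present point changes neither number.

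**2. Excess standard error in the normal model.** Omitting the factor multiplies the residual variance by 1 + p(1−p)d², with p(1−p) = 0.28·0.72 = 0.2016.
- d = 0.3: 1 + 0.0181; share of variance 0.0181/1.0181 = 1.8%; SE ratio √1.0181 = 1.009, about 0.9% too large.
- d = 0.5: 1 + 0.0504; share 0.0504/1.0504 = 4.8%; SE ratio √1.0504 = 1.025, about 2.5% too large.
- d = 0: no change.

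**3. What that does to the test.** Take a true effect that gives 90% power with the correct SE, that is 1.960 + 1.282 = 3.242 true SEs. An SE that is too large raises the effective critical value.
- d = 0.3: 1.960·1.009 = 1.978; power Φ(3.242 − 1.978) = Φ(1.264) ≈ 89.7%; loss about 0.3 points.
- d = 0.5: 1.960·1.025 = 2.009; power Φ(1.233) ≈ 89.1%; loss about 0.9 points.

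**4. Simulation, normal model.** One continuous component stands in for the bivariate model: 106 patients, strata of 30 and 76, blocks of 4 within stratum (block size assumed), treatment and baseline fitted, 8,000 replicates per setting.

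| Shift (residual SD) | SE excess without factor | Type I error, without / with | Power, without / with |
|---|---|---|---|
| 0 | 0% | 5.8% / 5.8% | 91.0% / 91.0% |
| 0.25 | 0.6% | 5.1% / 5.2% | 90.9% / 91.1% |
| 0.5 | 2.5% | 4.8% / 5.3% | 90.6% / 91.5% |
| 1.0 | 10% | 3.7% / 5.5% | 87.8% / 91.4% |

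A critical value of 1.96 was used in place of the t value, so type I error runs slightly above 5% throughout; simulation error on it is 0.2 to 0.3 points. At 0.5 SD under the null, the actual SD of the estimate is 0.155 with or without the factor, while the mean reported SE is 0.159 without it and 0.156 with it. The estimate is no more variable; only the reported error is larger.

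**5. Simulation, logistic model.** Same layout, 4,000 replicates.

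| Stratum OR | Type I error, without / with | Power, without / with | Mean SE of log OR (alternative), without / with |
|---|---|---|---|
| 1 | 4.3% / 4.4% | 85.2% / 85.2% | 0.492 / 0.496 |
| 1.5 | 4.6% / 4.9% | 84.3% / 84.7% | 0.490 / 0.497 |
| 2 | 4.3% / 4.6% | 83.6% / 84.5% | 0.488 / 0.500 |
| 4 | 4.1% / 5.1% | 79.7% / 82.7% | 0.478 / 0.515 |

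Here the SE is smaller, not larger, without the factor. The residual-variance argument of step 2 does not carry over: a logistic model has no residual variance to absorb, and omission costs power mainly because the conditional odds ratio is attenuated.

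**The case against.** The strongest reply is that a list of what a model will include is not a list of all it will include. The article defers to a Statistical Analysis Plan and condenses a fuller protocol, and either may carry the stratum. This stands in part: it lowers the severity. It does not remove the point, because the article is not silent on covariates. It states them for the primary model and ties the logistic model to the same set, and a statistician working from that text would fit treatment and baseline. For the secondary mixed models the reply is stronger, since there the text says much less; the change to them is asked for only so that the models agree.

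Second, the stratification has an operational purpose, equal arms within the sub-study, and nothing in the documents shows that consent is prognostic. Baseline ALP and bilirubin already carry biochemical severity. This stands, and is why the effect is stated conditionally.

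Third, the size is small, and the larger losses need a 1.0 SD shift or a stratum odds ratio of 4, beyond the range thought plausible here. This also stands.

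Fourth, adjustment is not wholly free: it adds one parameter in each of two equations, it changes what the logistic odds ratio is conditional on, and the article does not show that the resampling simulations behind 48 per arm included the term. These are reasons to write the change down carefully, not reasons against it.

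**Conclusion.** The stated models depart from the stated randomisation, and the departure is minor. For an assumed shift of 0.3 to 0.5 residual SD, the standard error in the bivariate normal model is about 1% to 2.5% too large and the cost is under about one point of power. If consent has no prognostic value beyond baseline, there is no effect. In the logistic model the consequence is mainly an attenuated conditional odds ratio and a small loss of power. These sizes rest on a stratum of about 30 of 106, on the assumed shift, and on a single-component model standing in for the bivariate one.

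A reader might infer that the primary standard error is simply wrong for the design, or that the test is invalid. The documents do not support that: the discrepancy exists only if consent is prognostic after baseline adjustment, and it then makes the test conservative, so false positives are not inflated. Nor do they support reading the article as ruling the stratum out of the final analysis, since the unseen analysis plan may add it.

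**What to change.** Before unblinding, state in the protocol and analysis plan that the biopsy-consent stratum, as used at randomisation, enters both component equations of the augmented binary model as a covariate. Obtain the normalisation rates and their odds ratio by averaging the model's predictions over the stratum. Add the same term to the logistic regression and note that its conditional odds ratio is then also conditional on stratum. Apply the adjustment to the secondary linear mixed models for consistency. If the factor is deliberately left out, say so and give the reason.

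The cost is one parameter per component equation, one in each other model, and the averaging step. No new data are needed, because consent to the sub-study is taken at screening and used for allocation. The sample size does not change.
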